| Trial setting                                                | 212-218         | The study will be conducted in Oliver Reginald Tambo district (Figure 1) within South Africa's Eastern Cape province (EC). This research will be conducted at the Nelson Mandela Academic Hospital, located in the King Sabata Dalindyebo subdistrict, and at the St Elizabeth Hospital, situated in the Ingquza Hill subdistrict.                                                                                                                                                                                                                                                                                                                                                                                                                                                                                                                                                                                                                                                                                                                                                                                                                                                                                                                                                                                                                                                                                                                                                                                                                      | 8-9   |

|                             |                        |                                                                                                                                                                                                                                                                                                                                                                                                                                                                                                                                                                                                                                                                                                                                       |        |

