|                                             |         | will be monitored through emotional check-ins, supervision meetings, and participant reports. All concerns will be documented, reviewed, and addressed following ethical guidelines for participant safety.                                                                                                                                                                                                                                                                                                                                                                                                                                        |       |
| Participant timeline                        | 252-255 | In the intervention group, four interventions will be implemented at one-month intervals, each followed by an evaluation of quality of life and mental health status outcomes. The four evaluations in the intervention group will run concurrently with those in the control group.                                                                                                                                                                                                                                                                                                                                                               | 10    |
| Sample size                                 | 286-299 | $n = \frac{(\sigma_1^2 + \sigma_2^2)(Z_{1-\alpha} + Z_{1-\beta})^2}{(\mu_1 - \mu_2)^2}$ 
The sample size was calculated using the equation, for a two-sided 95% confidence interval, where <math>\alpha = 0.05</math>, <math>Z_{1-\alpha} = 1.96</math>, and for 80% power, <math>Z_{1-\beta} = 0.84</math>. The mean difference <math>\mu_1 - \mu_2 = 1</math> and the standard deviation (<math>\sigma</math>) = 2. The sample size was calculated using a two-sample means formula, assuming a mean difference of 1 and a standard deviation of 2, which corresponds to a medium standardized effect size (Cohen's <math>d = 0.5</math>).
 | 12-13 |

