| Recruitment                                 | 305-310 | Participant recruitment will take place in collaboration with healthcare workers from the oncology units at Nelson Mandela Academic Hospital and St. Elizabeth Hospital. To raise awareness about the study and its benefits, informational sessions will be conducted within the hospitals, accompanied by posters displayed in key areas, such as the women's health units. Health promoters will actively engage potential participants, providing explanations about the study in local languages and assisting with the informed consent process.                                                                                             | 13    |
| Methods: Assignment of interventions |         |                                                                                                                                                                                                                                                                                                                                                                                                                                                                                                                                                                                                                                                    |       |
| Randomization:                              | 236-238 | A randomised control trial of 128 participants with a cervical cancer diagnosis from two hospitals (Nelson Mandela Academic and St Elizabeth hospitals) will be recruited for the intervention.                                                                                                                                                                                                                                                                                                                                                                                                                                                    | 9     |

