| Sequence generation                         | 284-287 | $n = \frac{(\sigma_1^2 + \sigma_2^2)(Z_{1-\alpha} + Z_{1-\beta})^2}{(\mu_1 - \mu_2)^2}$ 
The sample size was calculated by the Biostatistician using the equation for a two-sided 95% confidence interval, where <math>\alpha = 0.05</math>, <math>Z_{1-\beta} = 1.96</math>, and for 80% power, <math>Z_{1-\beta} = 0.84</math>. The mean difference <math>\mu_1 - \mu_2 = 1</math> and the standard deviation (<math>\sigma</math>) = 2
                                                                                                                                                                                                    | 12    |
|                                             | 317-359 | Cluster randomising at the hospital level (rather than individual level) will be employed to select patients with a cervical cancer diagnosis at both Nelson Mandela Academic and Saint Elizabeth hospitals to participate in a survey on their quality of life and their mental health status, specifically screening for depression and anxiety.                                                                                                                                                                                                                                                                                                 | 13-14 |
| Allocation concealment mechanism            | 337-359 | To ensure allocation concealment and minimise selection bias, the randomisation process will be managed independently by a designated biostatistician and data capturer who will not be involved in participant recruitment or data collection. The random allocation sequence will be securely stored in a password-protected electronic system. The interventions and data collection will be conducted independently at each hospital. Participants will be randomly assigned to two groups, with 64 participants in each of the intervention and control groups.                                                                               | 14    |

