|                                                           | 337,354-355           | Blinding will be achieved by ensuring that outcome assessors and data analysts remain unaware of group allocation throughout the data collection and analysis process. Limit the sharing of intervention materials or training across clusters until the study concludes.
The study will use separate WhatsApp groups, training sessions, and supervision structures for each arm.                                                                                                                                                                                                                                                                                                                                                                                                                                                                                                                                                                                                                                                                                                                                                                                                                                     | 14    |

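### The protocol states two incompatible units of randomisation, and the hospital-level one, with only two hospitals, would leave the treatment effect inseparable from the hospital difference

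*Protocol*

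**What the plan says.** All of this is in the protocol's SPIRIT 2025 checklist.

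- **Sequence generation:** "Cluster randomising at the hospital level (rather than individual level) will be employed to select patients with a cervical cancer diagnosis". The sentence goes on to name both hospitals and a survey of quality of life and mental health.
- **Allocation concealment mechanism** (the next row): "Participants will be randomly assigned to two groups, with 64 participants in each of the intervention and control groups". The same row says "The interventions and data collection will be conducted independently at each hospital".
- **Randomization:** "A randomised control trial of 128 participants with a cervical cancer diagnosis from two hospitals".
- **Trial setting:** the same two hospitals, in different subdistricts, and no others.
- **Blinding:** cluster language returns in "Limit the sharing of intervention materials or training across clusters until the study concludes". The row also plans separate messaging groups, training sessions and supervision for each arm, and discloses allocation only once baseline data are in.
- **Sample size:** "The sample size was calculated using a two-sample means formula, assuming a mean difference of 1 and a standard deviation of 2", at two-sided 5% and 80% power. No intracluster correlation or design effect appears.
- **Statistical methods:** t-tests, chi-squared, Wilcoxon and Fisher tests between arms, plus logistic regression. No hospital or cluster term is named.

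**The concern.** The unit of randomisation determines how the list is generated, which comparison is randomised and which analysis is valid. It has to be fixed in the protocol and cannot be left to a statistical analysis plan. Here two adjacent rows fix it in opposite ways.

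The conflict matters because the two readings lead to very different trials. Individual randomisation within two hospitals is an ordinary two-arm trial of 128 patients. Hospital-level randomisation of two hospitals to two arms has one cluster per arm, and neither more patients nor a cluster-adjusted model can repair that. Any difference between the hospitals that affects the outcomes would be reported as a treatment effect, with p-values that are too small.

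**Working it through.** **1. Reproduce the planned sample size.** Inputs from the Sample size row: mean difference 1, SD 2 in each arm, z values 1.96 and 0.84.

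n per arm = (2² + 2²) × (1.96 + 0.84)² / 1² = 8 × 7.84 = 62.72, so 63 per arm. The exact two-sample t-test gives 79.5% power at 63 and 80.1% at 64. The stated 64 per arm and 128 in total are therefore reproduced as an individually randomised design with no allowance for clustering.

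**2. Set the statements side by side.**

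| Checklist row | Unit implied |
|---|---|
| Sequence generation | Hospital, with individual level expressly excluded |
| Blinding (contamination control) | Cluster |
| Allocation concealment mechanism | Participant, 64 per arm |
| Sample size | Participant, independent observations |
| Statistical methods | Participant, no cluster term named |

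**3. Follow the hospital-level rule.** There are two hospitals and two arms, so each arm is one hospital. The arm indicator and the hospital indicator are then the same variable. The observed difference estimates treatment effect plus hospital difference, and nothing in the data separates the two. Between-hospital degrees of freedom are 2 − 2 = 0. This result does not depend on any assumed figure.

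**4. Illustrate the size.** The document gives no ICC, so a range is assumed, with m = 64 patients per hospital and hospital effects treated as random.

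- Design effect = 1 + (64 − 1) × ICC.
- Effective n per arm = 64 / design effect.
- With one hospital per arm, the t-test uses the within-hospital SD. The true variance of the difference therefore exceeds the one the test assumes by a factor V = design effect / (1 − ICC).
- True type I error = 2 × [1 − Φ(1.96 / √V)].

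| Assumed ICC | Design effect | Effective n per arm | V | True type I error of nominal 5% test |
|---|---|---|---|---|
| 0.01 | 1.63 | 39 | 1.65 | 12.7% |
| 0.02 | 2.26 | 28 | 2.31 | 19.7% |
| 0.05 | 4.15 | 15 | 4.37 | 34.8% |

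Even if the ICC were known in advance and allowed for, power for the planned effect would be about 60%, 47% and 28%.

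**5. Follow the individual rule.** With 64 per arm randomised within hospitals, each hospital contributes to both arms and step 1 applies: about 80% power for a standardised effect of 0.5.

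**The case against.** The strongest reply is that the hospital-level sentence is loosely worded. It speaks of selecting patients at both hospitals for a survey and never says that one hospital is intervention and the other control. The 64:64 assignment, the description as a randomised trial of 128 participants and the sample size formula all fit individual randomisation. The checklist also excerpts a longer manuscript, so fuller text may exist. This stands as far as intent goes: the document does not settle which design is meant. It does not remove the contradiction, because the sentence sits under Sequence generation, expressly excludes the individual level, and is echoed by the reference to clusters under Blinding.

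Three stronger readings are tempting, and the documents do not support them.

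- A reader might infer that the trial already is a two-hospital comparison. It is one only if the hospital-level sentence is followed.
- A reader might infer that concealment and assessor blinding are lost. All patients at a site would share its arm, so both could be weakened once that arm is known, the more so because health promoters help recruit. But disclosure is delayed until after baseline, and nothing says assessors are told which site has which arm. This is a risk, not an established failure.
- A reader might infer that case mix and usual care differ between the hospitals. The document reports neither by site. They may differ; aliasing means the trial could not tell.

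Contamination is a fair reason to think of clusters, but two hospitals are too few for that remedy.

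**Conclusion.** The contradiction is certain from the text and has to be resolved before randomisation. Which design is intended is not certain.

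If the hospital-level rule is followed, it is equally certain that arm is aliased with hospital, that no valid test of treatment exists, and that the 80% power claim does not apply. These conclusions rest only on there being two hospitals and two arms. The type I error figures of about 13%, 20% and 35% are illustrations that depend on the assumed ICCs of 0.01 to 0.05. If individual randomisation is meant, the sample size of 128 stands and the fault is confined to the cluster wording and the unstated handling of hospital.

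**What to change.** State one unit of randomisation throughout.

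- Delete the hospital-level sentence under Sequence generation and the reference to clusters under Blinding.
- State that individual patients are randomised 1:1, stratified by hospital, in concealed blocks, so that each hospital contributes to both arms.
- Include hospital as a factor in the between-arm analysis.

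This costs a protocol amendment and one stratified list. It needs no extra patients for the stated effect. The downside is some contamination within hospitals, partly mitigated by the arm-specific groups, sessions and supervision already planned. If contamination diluted the effect of 0.5 SD by an assumed 5%, 10% or 20% (to 0.475, 0.45 or 0.40 SD), power at 64 per arm would be about 76%, 71% or 61%. The team should decide whether to allow for that.

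If hospital-level allocation is really intended, withdraw the 80% power claim and the claim of a randomised comparison. Report instead a two-hospital comparison in which the treatment effect cannot be separated from the hospital difference.

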| Statistical methods                                       | 478-497               | The study will employ descriptive analyses of intervention participants' responses, utilizing means, standard deviations, medians, and interquartile ranges, as appropriate, based on the distribution's normality. Outcome measures of participants in the intervention group will be compared with those in the control group using an appropriate t-test, chi-squared test, Wilcoxon sum-ranked test, and/or the Fisher's exact test, depending on the normality of the distribution, and or the value of the expected frequencies. The study will compare pre- and post-interview guide summative scores using the paired t-test or the Wilcoxon signed-rank tests to ascertain patients' mental health status and quality of life (comparing post-test with pre-test scores) and whether mental health status and quality of life have changed after four months (comparing follow-up post-test with pre-test scores). Univariable and multivariable analyses will also be undertaken using logistic regression to determine the effectiveness of health promoters on the primary outcome measures and factors that are associated with mental health risk among cervical cancer survivors. The risk ratio (RR) will | 20-21 |

|                            |                           |                                                                                                                                                                                                                                                                                                                                                                                                                                                                                                                                                                                                                                                                                                                                                                                                                                                                                                                                                                                                                                                                          |              |

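### If allocation is individual, stratifying by hospital and adjusting for hospital and baseline score would add precision at almost no cost; the plan does neither

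*Protocol*

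**What the plan says.** All places are in the Protocol's SPIRIT 2025 checklist.

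- **Randomization row:** "A randomised control trial of 128 participants with a cervical cancer diagnosis from two hospitals".
- **Allocation concealment mechanism row:** "The interventions and data collection will be conducted independently at each hospital", followed by "Participants will be randomly assigned to two groups, with 64 participants in each of the intervention and control groups". Only the overall 64:64 total is fixed. Neither this row nor the Randomization, Sequence generation and Implementation rows mentions stratifying or blocking by hospital.
- **Sequence generation row:** it repeats the sample-size formula and then says "Cluster randomising at the hospital level (rather than individual level) will be employed". This conflicts with assigning individual participants.
- **Statistical methods row** (same text in the Protocol and statistical analysis plan row): "Outcome measures of participants in the intervention group will be compared with those in the control group using an appropriate t-test", or by chi-squared, rank-sum or Fisher's exact test. A multivariable logistic regression on the primary outcomes is also planned, with no covariates named.
- **Sample size row:** a two-sample means formula "for a two-sided 95% confidence interval" "and for 80% power", "assuming a mean difference of 1 and a standard deviation of 2".

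**The concern.** The protocol itself describes each hospital as a separate unit of delivery and measurement, and places the two hospitals in different subdistricts. That does not prove that outcomes differ between them, but it makes a difference plausible. Hospital is known before a patient is allocated, and baseline scores are collected before allocation is revealed. Both could be used, and the plan uses neither in the comparison of mean scores on which the trial is sized.

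Two things are at stake. First, an unstratified list lets the hospital mix differ between arms by chance, which adds random variation to the estimate. Second, that variation stays in the standard error of a pooled test, so 128 patients yield less precision than they could. Stratification is also a design choice: it has to be in place before the first allocation, and a later statistical analysis plan cannot restore it.

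**Working it through.** **Inputs from the Sample size row:** two-sided alpha 0.05 (z = 1.96), power 80% (z = 0.84), difference 1, SD 2. **From the Allocation concealment row:** 64 per arm.

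**Assumptions, not in the document:** a 50:50 hospital split unless stated otherwise, and a hospital difference of H points. With a within-hospital SD of 2, H = 1 is 0.5 SD and H = 2 is 1 SD.

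**1. The plan's own figure.** n per arm = (2² + 2²)(1.96 + 0.84)² / 1² = 8 × 7.84 = 62.72, so 63. The stated 64 is consistent with this. Power at 64 per arm is 80.7% (normal) or 80.1% (t-based).

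**2. Chance imbalance on an unstratified 64:64 list.** The number of patients from one hospital in the intervention arm is hypergeometric (N = 128, K = 64, n = 64).
- Variance = 64 × 0.5 × 0.5 × 64/127 = 8.06, so SD = 2.84. The 95% range is about 26 to 38 of 64.
- The between-arm difference in hospital share has SD 2 × 2.84/64 = 0.089. The 95% limit is 1.96 × 0.089 = 0.174, about 17 percentage points. A difference of 12.5 points or more occurs in about 22% of allocations.
- The estimate moves by H times that difference. Its 95% limits are ±0.17 for H = 1 and ±0.35 for H = 2, against a target of 1. These shifts average to zero.

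**3. Effect on power if SD 2 is the within-hospital SD.** Variance inflation = 1 + p(1 − p)H²/4, where p is the share from one hospital. At p = 0.5:

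| Hospital difference | Inflation | SE increase | Power, normal | Power, t-based | n per arm needed |
|---|---|---|---|---|---|
| 0.5 SD (H = 1) | 1.0625 | 3.1% | 78.3% | 77.7% | 67 |
| 1 SD (H = 2) | 1.25 | 11.8% | 71.6% | 70.9% | 79 |

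With an 80:20 split, the normal-approximation powers are 79.2% and 74.7%.

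**4. If SD 2 is the total SD over both hospitals.** The planned 80.7% stands. A hospital term at H = 1 removes 0.25 × 1² from the variance of 4, leaving a within-hospital SD of √3.75 = 1.94. Power becomes 83.2%.

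**5. Validity of the pooled test.** Simulation with 20,000 trials per scenario, p = 0.5, unstratified allocation:
- The pooled t-test has type I error between 4.9% and 5.0%, and a mean estimate of 1.00 when the true difference is 1, for both H = 1 and H = 2.
- Its power is 77.7% (H = 1) and 71.1% (H = 2). With a hospital term it is 79.9% and 80.1%.

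**6. Stratifying without adjusting.** Stratification removes the between-hospital variation from the estimate, but the pooled test leaves it in the standard error. Type I error = 2(1 − Φ(1.96 × √inflation)), which is 4.3% at 0.5 SD and 2.8% at 1 SD. The simulation gives 4.5% and 2.9%. The trial as written is not stratified, so this does not describe the current plan. It shows only why the two changes belong together.

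No figure is given for the baseline score. Its gain depends on the correlation between baseline and follow-up, which the document does not state.

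**The case against.** **The premise may not hold.** The Sequence generation row says that hospitals are randomised. With two hospitals and two arms, hospital and treatment would be inseparable, and neither separate lists nor a hospital term would help. This stands. The point applies only if the conflict is resolved towards individual allocation.

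**An adjusted analysis is already planned.** The multivariable logistic regression could include hospital, and a covariate list is commonly left to the statistical analysis plan. This stands in part: silence on those covariates is no fault. But logistic regression needs a binary outcome. It does not adjust the mean difference that the sample size rests on, and the method stated for comparing scores is a pooled test.

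**The analysis is valid as it is.** A reader might infer that hospital imbalance biases the result or raises the false-positive rate. The plan does not support either inference. Under unstratified randomisation the shifts average to zero and the pooled standard error already covers them. For the same reason, the shift in step 2 and the power loss in step 3 are one variance seen from two sides and must not be added together.

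**The loss may be small or nil.** This also stands. The document gives no hospital difference and no hospital split, and does not say whether SD 2 is a within-hospital or a total SD. On the last reading nothing is lost against plan.

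**Conclusion.** This is a free improvement, conditional on individual allocation. It is not an error that threatens validity. On the 64:64 allocation the protocol states no stratification by hospital, and its between-arm tests of the continuous scores ignore both hospital and baseline score. The consequence is lost precision.

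Its size rests on assumptions. With a 50:50 split and a within-hospital SD of 2, power is about 78% at a 0.5 SD hospital difference and about 71% at 1 SD, against about 80% planned. With SD 2 as the total SD, planned power holds and a hospital term would lift it to about 83% at a 0.5 SD difference. To call the trial underpowered on this ground would go beyond what the document shows. The firmer half of the point is stratification, because it cannot be added after allocation has begun.

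**What to change.** 1. Reconcile the hospital-level cluster statement in the Sequence generation row with the individual 64:64 assignment in the Allocation concealment row. The steps below apply only if allocation is individual.
2. In the Sequence generation row, state that the biostatistician generates a separate permuted-block list for each hospital.
3. In the Statistical methods row and its copy in the Protocol and statistical analysis plan row, make the primary between-arm comparison of the continuous scores a linear model with arm, hospital and baseline score. For binary outcomes, use a test stratified by hospital.
4. Make changes 2 and 3 together, since stratifying while keeping the pooled test would make that test conservative.

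The cost is a sentence or two in each place, one degree of freedom for each added covariate, and slightly more work in running two lists. No extra patients are needed, and baseline scores are already to be collected.

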|                                                           | 339                   | The allocation will be revealed only after the baseline data collection is complete.                                                                                                                                                                                                                                                                                                                                                                                                                                                                                                                                                                                                                                                                                                                                                                                                                                                                                                                                                                                                                                                                                                                                      | 14    |

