| Data management                                           | 474-477               | Data from baseline and post-intervention outcomes assessments will be captured electronically using a secure data management platform with built-in validation checks to ensure accuracy and minimize data entry errors. The data will then be exported to SPSS (Statistical Package for Social Sciences), software version 29                                                                                                                                                                                                                                                                                                                                                                                                                                                                                                                                                                                                                                                                                                                                                                                                                                                                                            | 20    |

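### The primary scores are compared between arms without baseline adjustment; the test is valid, but adjusting for the baseline already collected would add precision at no cost

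*Protocol*

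**What the plan says.** The Outcomes row of the Protocol names quality of life, PHQ-9 and GAD-7 as primary; the Data collection methods row gives WHO-QoL-BREF as the quality-of-life instrument.

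Baseline values will exist and will be uninfluenced by knowledge of the arm. The Blinding row says "The allocation will be revealed only after the baseline data collection is complete", and the Data management row says "Data from baseline and post-intervention outcomes assessments will be captured electronically".

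The between-arm analysis is in the Statistical methods row and is repeated in the Protocol and statistical analysis plan row: "Outcome measures of participants in the intervention group will be compared with those in the control group using an appropriate t-test". Rank-sum, chi-squared and Fisher's exact tests are the alternatives. Baseline enters by name only through paired pre-post tests. A multivariable logistic regression is also planned, with no covariates listed and the risk ratio as the measure of association.

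The sample size assumes a comparison of two means: "The sample size was calculated using the equation, for a two-sided 95% confidence interval", "and for 80% power", and "assuming a mean difference of 1 and a standard deviation of 2, which corresponds to a medium standardized effect size". The Allocation concealment row describes random assignment of participants, "with 64 participants in each of the intervention and control groups". The Sequence generation row instead describes randomising clusters at hospital level, and the trial has two hospitals.

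**The concern.** A patient's baseline score on a scale is usually a good predictor of her later score on it. An arm comparison that leaves it out treats that predictable variation as noise, so the confidence interval is wider than it need be. Any chance difference between the arms at baseline also passes in part into the estimated effect.

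Neither of the other planned analyses supplies the adjustment. The paired tests look at change within patients and do not contrast the arms. The logistic model needs a binary outcome, so even with baseline added it would not yield an adjusted difference in means, which is the quantity the trial was sized on.

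**Working it through.** **Inputs from the Protocol.** Two-sided alpha 0.05 (Z = 1.96), power 80% (Z = 0.84), difference 1, SD 2 (Sample size row); 64 per arm (Allocation concealment row).

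**Assumptions not in the Protocol.** The within-arm correlation r between baseline and follow-up, taken as 0.3 to 0.7; a baseline SD equal to the follow-up SD of 2; individual randomisation.

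**Step 1: reproduce the plan's figure.** The formula gives n = (4 + 4) × (1.96 + 0.84)² / 1² = 62.7, so 63 per arm. The t-test calculation gives 63.8, so 64. Power at 64 per arm is 80.1% by the t-test (80.7% by the normal approximation). The stated sample size and the stated unadjusted test agree.

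**Step 2: adjust for baseline at the same sample size.** The residual SD becomes 2 × √(1 − r²). The standard error of the arm difference is that SD × √(2/64). The unadjusted sample size with equivalent precision is 64 / (1 − r²) per arm.

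| r | Residual SD | SE of difference | Power at 64 per arm (t) | Equivalent unadjusted n per arm |
|---|---|---|---|---|
| 0 (unadjusted) | 2.000 | 0.354 | 80.1% | 64 |
| 0.3 | 1.908 | 0.337 | 83.7% | 70 |
| 0.4 | 1.833 | 0.324 | 86.5% | 76 |
| 0.5 | 1.732 | 0.306 | 90.0% | 85 |
| 0.6 | 1.600 | 0.283 | 93.9% | 100 |
| 0.7 | 1.428 | 0.252 | 97.6% | 125 |

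A simulation of 20,000 trials per value of r agrees. Unadjusted against adjusted power was 80.1% and 83.2% at r = 0.3, 80.5% and 89.9% at r = 0.5, and 80.6% and 97.5% at r = 0.7.

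**Step 3: effect of a chance imbalance.** The baseline difference between arms has SE 2 × √(2/64) = 0.354. Given an observed imbalance, the unadjusted estimate shifts by r times that imbalance. One SE therefore moves it by 0.3 × 0.354 = 0.11 to 0.7 × 0.354 = 0.25 points, against a target difference of 1.

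The extreme case needs its frequency beside it. At r = 0.5 and a 2-SE imbalance, the test statistic is centred at 0.5 × 2 = 1 under the null with variance 1 − 0.25 = 0.75. The chance that it exceeds 1.96 in absolute value is 0.134. An imbalance that large or larger arises in about 5% of trials, and averaged over all imbalances the false-positive rate is the nominal 5%.

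**Step 4: is a change-score t-test enough?** Its SD is 2 × √(2(1 − r)). By the normal approximation, power at 64 per arm is 66.7% at r = 0.3, 80.7% at r = 0.5 and 95.5% at r = 0.7. ANCOVA on the same basis gives 84.3%, 90.4% and 97.7%. The change score is never better here, and below r = 0.5 it is worse than no adjustment.

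**The case against.** The strongest reply is that nothing is broken. Under individual randomisation the two-sample t-test is valid, the sample size was computed for it, and 64 per arm delivers the planned power. That stands, and it rules out two readings that a reader might infer. One is that the trial is underpowered on its own assumptions; step 1 shows that it is not. The other is that chance imbalance biases the estimate, or that the test runs at a 13% false-positive rate. Randomisation makes the unadjusted estimate unbiased on average, its standard error already allows for imbalance, and the 13% belongs only to the rare case in step 3.

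The size of the gain also rests on figures that the Protocol does not give. At r = 0.3 the gain is only three to four percentage points of power. The difference of 1 and SD of 2 are not tied to any one of the three scales. Both limits stand.

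It can also be said that the wording leaves room: outcome measures might mean change scores, and the multivariable model might include baseline. Neither is stated. Step 4 shows that change scores are not a full substitute, and the logistic model targets a different quantity. Nor is the matter simply left to an unseen SAP, since the Protocol itself names the test.

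The objection with most force concerns design. If the two hospitals are the randomised units, arm and hospital are the same variable. A hospital term would then be collinear with arm, and baseline adjustment would not separate the two. This stands and limits the remedy.

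**Conclusion.** This is a free improvement and does not correct an error. The Protocol fixes an unadjusted comparison of scores for which it will hold baseline values taken before allocation is revealed. With individual 64/64 randomisation, the planned test keeps its 80% power. Baseline adjustment would bring that to about 84% to 98% for r between 0.3 and 0.7, with a confidence interval narrower by about 5% (1 − 1.908/2) to 29% (1 − 1.428/2). It would also remove the conditional effect of a chance imbalance. The figures depend on the assumed r; those for imbalance also depend on a baseline SD of 2. None of them applies if hospitals are the randomised units.

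**What to change.** First reconcile the Sequence generation and Allocation concealment rows on whether hospitals or participants are randomised. With two hospitals as the units, neither the present test nor the model below can separate arm from hospital.

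Then, in the Statistical methods row and the Protocol and statistical analysis plan row:

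- Make the between-arm analysis of each primary score a linear model (ANCOVA) of the score at one named evaluation, for example the last of the four monthly ones, on arm and the baseline value of the same scale.
- Report the adjusted mean difference with its 95% confidence interval.
- Include a hospital term only if participants are randomised individually within hospitals.
- Keep the unadjusted, rank-based and paired tests as supportive; the rank-based test then serves as the check for markedly non-normal scores.

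The analysis change costs a few lines of wording. It needs no further data or patients, and the planned software fits the model directly. Reconciling the unit of randomisation is a separate task that the trial needs in any case.
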